## Abstract

**Introduction:**

Irritable bowel syndrome (IBS) is a common chronic functional gastrointestinal disorder that presents with abdominal pain/discomfort and altered bowel patterns. IBS has multiple potential causes for which conventional medicines have had limited success, resulting in a significant number of patients who do not sensitively respond to pharmacotherapy for a period of 12 months and who develop a continuing symptom profile (described as refractory IBS) and seek help through (non)pharmacological treatments. The aim of this study is to investigate the efficacy and safety of acupuncture therapy for refractory IBS on the basis of conventional treatments.

**Methods and analysis:**

A total of 170 eligible patients who meet the Rome IV criteria for refractory IBS will be randomly allocated to receive acupuncture or sham acupuncture. Each patient will receive 12 sessions of acupuncture over 4 weeks and a 4-week follow-up. The primary outcome will be the IBS Symptom Severity Score. Secondary outcomes will include the proportion of participants experiencing adequate relief of global IBS symptoms, the weekly frequency of defecation, the stool properties assessed by the Bristol Grading Scale, the Work and Social Adjustment Scale, the IBS-Quality of Life score, and the Self-Rating Depression Scale and Self-Rating Anxiety Scale anxiety and depression scores. Outcome measures will be collected at baseline, 2 and 4 weeks of the intervention, and 6 and 8 weeks after the intervention. Categorical variables will be compared with Fisher’s exact test or the Wilcoxon rank-sum test, and continuous variables will be compared using Student’s t-test or the Wilcoxon rank-sum test.

**Ethics and dissemination:**

The entire project has been approved by the ethics committees of Beijing University of Chinese Medicine (2020BZYLL0507) and Sichuan Province Regional Institution for Conducting Research on Traditional Chinese Medicine (2020KL-025). The outcomes of the trial will be disseminated through peer-reviewed publications.

**Trial registration number:**

NCT04276961.

Strengths and limitations of this studyThis is the first multicentre randomised controlled trial verifying the benefit of acupuncture added to usual treatments for refractory irritable bowel syndrome (IBS).A sham acupuncture group will be used to investigate the placebo effect of acupuncture.This trial meets the methodological demand of adequate concealment of randomised group allocations, outcome assessors and statisticians.Participants will be screened for eligible refractory IBS at baseline through three rigorous phases.A limitation of this trial is that since a rigorous study design was developed to identify which patients with IBS are ‘refractory’, we must fully consider the differences in the severity of symptoms, the duration of symptoms, the dietary interventions or advice provided, and even the conventional pharmaceutical treatments provided.

## Introduction

Irritable bowel syndrome (IBS) is the most common functional gastrointestinal disorder worldwide.^1^ Epidemiological data show that the prevalence of IBS is approximately 5%–6% in China,^2^ 9.5%–9.8% in Asia^3^ and 11% worldwide,^4^ which indicates that IBS is a major public health issue. Owing to the complex pathogenesis of IBS, several pathogenic factors (genetic and environmental factors, visceral hypersensitivity, abnormal gut motility, postinfectious inflammatory mechanisms, gut microbiota changes, psychological morbidity, and physical and emotional factors) have been proposed as possible causes.^5^ Hence, the study of patients with IBS is still a challenge.

Furthermore, in clinical practice, patients with IBS complain about various symptoms, such as changes in bowel habits, abdominal pain, diarrhoea or constipation, and meteorism, which considerably worsen their quality of life (QOL). The Rome IV criteria suggest that IBS treatment is selected on the basis of the symptom type (abdominal pain, diarrhoea, etc).^1^ Simultaneously, patients are stratified into four subtypes: constipation-predominant IBS, diarrhoea-predominant IBS, mixed IBS and unclassified IBS. Many medications for treating IBS-related symptoms have been developed for various IBS subtypes, including antispasmodics, psychotropic agents, bulking agents, 5-HT (5-hydroxytryptamine) receptor antagonists, antibiotics, probiotics and so on. Although 5-HT3 antagonists, 5-HT4 agonists, antispasmodics and alosetron have been shown to be useful for the treatment of IBS,^6^ regrettably, some drugs, such as guanylate cyclase-C agonists and loperamide, have been proven to be inadequate for relieving symptoms.^6 7^ Similarly, some psychological therapies, such as hypnotherapy, relaxation therapy and cognitive–behavioural therapy, have been proven to be effective treatments for IBS.^8^ Even when these available treatments are used, symptoms can persist for more than 12 months in some patients with IBS. These patients with IBS can be considered therapy resistant (refractory).^9 10^ Therefore, novel treatment options for IBS, especially refractory IBS, are urgently needed.

Recently, there has been an increase in the use of non-pharmacological therapies, including acupuncture, which is widely accepted as an effective alternative treatment for gastrointestinal disorders in clinical practice.^11^ According to reviews of the literature, acupuncture is not only satisfactory for IBS but may also be more effective than pharmacological therapies in alleviating the symptoms and QOL, with its effects lasting up to 12 weeks,^12^ even sustaining benefits over a period of 12 months postrandomisation.^13 14^ However, there are still limitations within previous studies, including small sample sizes, poor quality of the trials and lack of detailed assessments of symptom improvement, such as social activity scales and psychological questionnaires. Meanwhile, few studies have been designed for investigating the treatment of refractory IBS with acupuncture. Therefore, the main objective of this trial is to evaluate, on the basis of conventional treatments, the efficacy of acupuncture versus sham acupuncture for refractory IBS in terms of symptom management.

## Methods/design

### Study design

This multicentre randomised controlled trial (RCT) will be conducted at six hospitals in China: Dongzhimen Hospital Affiliated to Beijing University of Chinese Medicine; Dongfang Hospital Affiliated to Beijing University of Chinese Medicine; Third Hospital Affiliated to Beijing University of Chinese Medicine; Beijing Hospital of Traditional Chinese Medicine Affiliated to Capital Medical University; Clinical Medicine College/Teaching Hospital Affiliated to Chengdu University of Traditional Chinese Medicine; and Third Hospital/Acupuncture and Tuina School Affiliated to Chengdu University of Chinese Medicine. The study has been approved by ethics committees and registered on www.clinicaltrials.gov on 19 February 2020. The study protocol will follow the principles of the Declaration of Helsinki and clinical research to Good Clinical Practice (GCP) guidelines, and will be reported based on SPIRIT (Standard Protocol Items: Recommendations for Interventional Trials) 2013 Checklist.^15^ The checklist is provided in the online supplemental additional file 1.

10.1136/bmjopen-2020-045655.supp1Supplementary data

Eligible patients will be randomly divided into two groups comprising participants who will receive 1 week of washout, 12 sessions over 4 weeks of treatment and 4 weeks of post-treatment follow-up. Outcomes will be assessed at baseline, during the treatment and at the end of the follow-up. A flow diagram of the trial is shown in figure 1.

**Figure 1 F1:**
[figure not shown]
Trial flow diagram. IBS, irritable bowel syndrome.

### Patient recruitment

Step 1: Patients meeting the Rome IV IBS criteria (table 1) will be primarily recruited from the outpatient centres of the six participating hospitals. The mode of recruitment will also include advertisements through hospital social media sites (WeChat subscription), posters, Sojump, flyers about this trial, outpatient clinics and publicity at surrounding community service centres. Step 2: Patients (1) with IBS-related symptoms lasting for at least 12 months and (2) without a response to currently available IBS treatments, such as antibiotics or probiotics, dietary changes, antidepressants or psychotherapies, will be included.^16–18^ Clinicians will primarily select patients with suspected refractory IBS for further detailed assessment. Step 3: A clinical research assistant will identify eligible participants for this trial according to the following rigorous inclusion and exclusion criteria (box 1 and box 2). All patients will voluntarily agree to participate and will sign an informed consent document before randomisation.

**Table 1 T1:** Rome IV criteria: irritable bowel syndrome^45^

Diagnostic time frame	Symptom description	Symptoms
≥3 months of persistent symptoms with symptom onset at least 6 months before diagnosis ≥1 day/week	Abdominal pain	Recurrent association (two or more) of the following criteria: Related to defecation Associated with a change in the form of stool Associated with a change in the frequency of stool

Box 1Inclusion criteriaItemsAdults aged 18–70 years (either sex).Fulfilment of the Rome IV criteria for IBS.Patients with normal results of tests for occult blood in stool within the past month.Age above 50 years and normal results of colonoscopy within the previous year.Presence of symptoms for ≥12 months.Absence of response to a minimum of 6 weeks of dietary intervention or advice.Absence of response to an adequate dose of at least one conventional pharmacological agent tried for a minimum of 6 weeks.Signing of the written informed consent form.

Box 2Exclusion criteriaItemsPrevious colonoscopy, meal barium fluoroscopy, abdominal ultrasound and other examinations revealing severe intestinal organic lesions (including but not limited to ulcerative colitis, familial multiple intestinal polyps and colorectal cancers).The presence of one or more of the following warning symptoms: unexplained rectal bleeding, a positive faecal occult blood test result; anaemia, abdominal mass, ascites, fever and emaciation.The presence of other severe medical conditions, such as cardiovascular disease, endocrine disorders, hepatic dysfunction, renal diseases and cognitive disorders that can affect the outcome assessment results.Unconsciousness, inability to express subjective symptoms of discomfort and clearly diagnosed severe mental disorders.An unstable psychological state or accompanying psychological disorders (SDS>56).Present history of pregnancy or lactation.Acceptance of acupuncture treatment in the last 3 months.Difficulties in attending the trial, such as fear of acupuncture.

### Randomisation/allocation

A block randomisation sequence for multiple centres will be generated by an independent professional statistician (Linkermed Tech) using Statistical Analysis System (SAS) software. All eligible participants will be randomly stratified into the acupuncture group or sham acupuncture group in a 1:1 ratio. Simultaneously, we plan to cooperate with a remote central web-based randomisation system. The clinical research assistant will be responsible for enrolling patients, screening patients, obtaining informed consent, requesting randomisation and collecting data.

### Blinding

Patients as well as research assistants, outcome assessors and statisticians will be blinded to the group assignment. However, due to the nature of acupuncture, the acupuncturists providing the interventions cannot be blinded. To minimise known sources of bias, the number/or location of the acupuncture points and manipulation of needles will be similar in the acupuncture and sham acupuncture groups, thereby optimising the blinding of subjects. Similarly, to avoid the subjective bias of researchers and subjects, the data analysis of the whole experiment will adopt a third-party blind evaluation. The participant’s allocated intervention will not be revealed until the statistical analysis reports are finalised.

### Interventions

To ensure the safety and proper operation of acupuncture, all acupuncturists will participate in the standard operation process (SOP) of skin disinfection, location of acupoints and non-acupoints, fundamental puncture and needle manipulations before the trials. Treatments will be performed by licenced acupuncturists who have at least 3 years of experience in acupuncture. Acupuncture will be discontinued if the patients experience any adverse events (AEs) after acupuncture. The schedule of enrolment, interventions, assessments and participant visits is shown in figure 2.

**Figure 2 F2:**
[figure not shown]
Schedule of enrolment, intervention and assessments of this study protocol. IBS, irritable bowel syndrome; SAS, Self-Rating Anxiety Scale; SDS, Self-Rating Depression Scale; TAU, treatment as usual.

### Treatment as usual

Treatment as usual (TAU) is defined as the continuation of current therapeutic agents prescribed by a general practitioner or gastroenterologist. All patients will continue TAU during the study period. Any changes in the medications of individual participants will be recorded on diary cards.

### Acupuncture group

Patients allocated to the acupuncture group with disposable and sterile acupuncture needles (length: 25–40 mm, diameter: 0.30 mm; Hwatuo, Suzhou, China) will receive treatment with acupuncture three times a week for 4 weeks for a total of 12 treatment sessions. Based on traditional Chinese medicine (TCM) theory and our clinical experience, the prespecified acupoints used here will include bilateral *Tianshu (ST25)*, *Shangjuxu (ST37)*, *Zusanli (ST36)* and *Neiguan (PC6*) (table 2 and figure 3). The exact location and depth of needling for each point will be determined based on the 2006 People’s Republic of China National Standard: The Name and Location of Acupoints (GB/T 12346-2006).^19^ After insertion, manipulations of twirling, lifting and uniform reinforcing-reducing manipulation will be performed on all needles to elicit ‘deqi’. The compositional sensation of ‘deqi’ includes numbness, soreness, distention, aching and heaviness, which are believed to be an essential component for acupuncture efficacy.^20^ Then, the needles will be removed after a 30 min session with clean cotton balls to prevent bleeding.

**Table 2 T2:** Locations of acupoints in the acupuncture group

Acupoints		Locations
Tianshu (ST25)	Bilateral	On the same level of the umbilicus, and 2 cun* lateral to the anterior midline
Shangjuxu (ST37)	Bilateral	6 cun directly below Dubi (ST35), and one finger-breadth lateral to the anterior border of the tibia
Zusanli (ST36)	Bilateral	3 cun directly below Dubi (ST35), and one finger-breadth lateral to the anterior border of the tibia
Neiguan (PC6)	Bilateral	On the line joining Daling (PC7) and Quze (PC3), between the tendons of palmaris longus and flexor carpi radialis, 2 cun above the transverse crease of the wrist

*1 cun (≈20 mm) is defined as the width of the interphalangeal joint of patient’s thumb.

**Figure 3 F3:**
[figure not shown]
Locations of acupoints and non-acupoints.

### Sham acupuncture group

The participants in the sham acupuncture group will also receive the same treatment duration and frequency of sessions as the real acupuncture group. Similarly, sham acupuncture will be performed at predefined bilateral sites (non-acupoints 1–4) not corresponding to acupuncture group traditional points or meridians, penetrating to the same depth but without needle manipulation for ‘deqi’ (table 3 and figure 3). Patients will be informed of the two types of acupuncture as follows: ‘in this trial, different types of acupuncture will be compared, but another approach might not target your additional symptoms.’ This language will be used to avoid deception while unifying the simulation conditions of the two groups as much as possible, mixing real and sham points, and this might enhance patient compliance.

**Table 3 T3:** Locations of non-acupoints in the sham acupuncture group

Non-acupoints		Locations
Non-acupoint 1	Bilateral	In the middle of Daheng (SP15) and Zhangmen (LR13) points (lateral aspect)
Non-acupoint 2	Bilateral	In the medial arm on the anterior border of the insertion of the deltoid muscle at the junction of the deltoid and biceps muscles
Non-acupoint 3	Bilateral	On the same level 1–2 cun* outboard lateral of the ST36
Non-acupoint 4	Bilateral	In the middle of the medial epicondyle of the humerus and the styloid process of ulna

*1 cun (≈20 mm) is defined as the width of the interphalangeal joint of patient’s thumb.

## Outcomes

### Primary outcome

#### IBS Symptom Severity Score

According to previous assessment recommendations,^21^ the IBS Symptom Severity Score (IBS-SSS) is a validated scoring system that relates to the severity of abdominal pain (IBS-SSS1), frequency of abdominal pain (IBS-SSS2), bloating (IBS-SSS3), satisfaction with bowel habits (IBS-SSS4) and disruption of QOL (IBS-SSS5), and will be used as the primary outcome of this trial. Participants will respond to each question on a 100-point Visual Analogue Scale. Each of the five questions generates a maximum score of 100 points, and the total is scored from 0 to 500, with higher scores indicating severe symptoms: normal (<75), mild IBS (75–175), moderate IBS (175–300) and severe IBS (>300). IBS-SSS will be assessed at baseline and 2, 4, 6 and 8 weeks after randomisation.

### Secondary outcomes

#### Adequate relief of global IBS symptoms

During our treatment period, patients will respond weekly to the question: ‘In regard to all your symptoms of IBS, as compared with the way you felt before you added acupuncture therapy on the basis of conventional treatments, have you, in the past 7 days, had adequate relief of your IBS symptoms?’ (yes/no). ‘Yes’ will be regarded as a positive response to treatment.^22^

#### Bristol Stool Form Scale

The Bristol Stool Form Scale classifies stool consistency into seven types encompassing complications from constipation to diarrhoea.^23^ In this trial, participants will be asked to record the weekly defecation types and scores. The scores obtained from the Bristol scale will be assessed at baseline and weeks 2, 4, 6 and 8.

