#### The weekly frequency of defecation

The frequency of bowel movements during the week before each visit will be assessed at baseline and 2, 4, 6 and 8 weeks after randomisation. A normal defecation is defined as a daily stool frequency ≤3 times and a stool consistency of type (like a sausage or snake; smooth and soft).^24^

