### Sample size and statistical analysis

Based on two sample size mean literature data speculation and previous clinical experience,^12 31^ we anticipate the scores of two acupuncture groups on the continuation of current medications as follows: responders can improve refractory IBS on the IBS-SSS with scores of 30 and 15, respectively. The SD is set at 15, and the ratio between the acupuncture and sham acupuncture groups is 1:1. The sample size is calculated with a 20% type II error rate (80% power) and 5% type I error. The superiority trial will be adopted to minimise the difference between the two groups, and a 10-point is expected. In total, a sample size of 154 (77 patients in each group) is estimated. Allowing for 10% loss to follow-up, the sample size expands to 85 patients in each group.

All analyses will be performed using the intent-to-treat (ITT) and the per-protocol (PP) populations. ITT requires all participants to receive a baseline assessment of the primary outcome and at least one acupuncture session or one sham acupuncture administration. Missing values will be imputed through the multiple imputation method. The PP population is usually defined as patients who complete at least 80% of the treatment protocol without major protocol violations. The primary outcome will be assessed using analysis of covariance and adjusted for baseline total IBS-SSS. For other secondary outcomes, continuous variables will be analysed using Student’s t-test or the Wilcoxon rank-sum test, and data will be represented as the mean±SD or median; categorical variables will be calculated using Fisher’s exact test or the Wilcoxon rank-sum test, and data will be presented as frequencies (percentages). In terms of efficacy factors, other covariates, such as age, sex, disease duration, conventional pharmacological agent classification and so on, will be considered for further revision. The differences in blinding and AEs between the groups will be compared using the χ^2^ test. Moreover, we have decided to carry out a subgroup analysis based on patients with IBS subtypes, avoiding a heterogeneous patient population that may affect the efficacy results.

Statistical analysis of all data in this study will be performed by a specialised third-party statistician evaluation. SAS, V.8.2 statistical software (SAS Institute), will be used for data analysis. A two-sided p<0.05 will be considered statistically significant.

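### Bristol score and weekly stool frequency are pooled over IBS subtypes that improve in opposite directions, so the comparison is diluted by subtype mix and its sign cannot be read as benefit or harm

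*Protocol article*

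**What the plan says.** **Population.** The Introduction lists the subtypes: "patients are stratified into four subtypes: constipation-predominant IBS, diarrhoea-predominant IBS, mixed IBS and unclassified IBS". The inclusion criteria (Box 1) ask for "Fulfilment of the Rome IV criteria for IBS", and neither Box 1 nor Box 2 restricts subtype. The planned subtype subgroup analysis confirms that a mixed sample is expected.

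**Outcomes.** The section on the Bristol Stool Form Scale describes a two-directional measure: "The Bristol Stool Form Scale classifies stool consistency into seven types encompassing complications from constipation to diarrhoea". It then says "The scores obtained from the Bristol scale will be assessed at baseline and weeks 2, 4, 6 and 8". The section on weekly frequency says "The frequency of bowel movements during the week before each visit will be assessed at baseline and 2, 4, 6 and 8 weeks after randomisation". Neither section names a direction of benefit. The frequency section does define a normal stool, "A normal defecation is defined as a daily stool frequency ≤3 times and a stool consistency of type", followed by a description of a smooth, soft form, but no stated analysis uses that definition.

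**Analysis.** Sample size and statistical analysis states: "For other secondary outcomes, continuous variables will be analysed using Student’s t-test or the Wilcoxon rank-sum test", summarised as mean with SD or as median. Categorical variables go to Fisher's exact test or the rank-sum test. The same section plans a subgroup analysis by IBS subtype without saying which outcomes it covers.

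**The concern.** On both measures the good result lies in the middle. A constipated patient who improves moves up the Bristol scale and passes more stools. A diarrhoeal patient who improves does the reverse. A pooled comparison of raw values sets one change against the other.

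Two things follow. First, the size of the pooled difference depends on the proportions of the subtypes as well as on the treatment, so a treatment that helps everyone may show little. Second, the sign is ambiguous: a lower pooled mean may be relieved diarrhoea or worsened constipation. The rank-sum test is also directional, so choosing it does not remove either problem.

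**Working it through.** The article gives no power figure for these two outcomes, so there is none to reproduce. Its 77 per arm was derived for the IBS-SSS and is used here only as the arm size.

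**Inputs from the article:** 77 per arm before allowance for loss; two-sided 5% level; t-test or Wilcoxon; seven Bristol types.

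**Assumed inputs, not in the article:** only constipated and diarrhoeal patients; Bristol means of 2 and 6 under sham; SD 1 within subtype; acupuncture moves every patient 1 type (or 0.5) towards type 4, the midpoint of the scale; sham moves nobody.

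**Step 1, dilution.** With effect *e* and diarrhoeal share *p*, the pooled mean difference is e × [(1 − p) − p] = e × (1 − 2p). For e = 1 this is 0 at p = 0.5, −0.4 at 0.7, −0.6 at 0.8 and −1 at 1. The same factor applies to changes from baseline.

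**Step 2, noise.** Pooling also adds the spread between subtypes. The subtype means are 4 apart under sham and 2 apart under acupuncture (e = 1), so the variances are 1 + 16p(1 − p) and 1 + 4p(1 − p).
- p = 0.7: variances 4.36 and 1.84; SE = √(6.20/77) = 0.284; 0.4/0.284 = 1.41; power about 29%.
- p = 0.8: variances 3.56 and 1.64; SE = √(5.20/77) = 0.260; 0.6/0.260 = 2.31; power about 64%.
- p = 1: SE = √(2/77) = 0.161; 1/0.161 = 6.2; power about 100%.

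**Step 3, simulation.** 4,000 trials per cell. Where a range is shown, it spans scores rounded and clipped to types 1–7 and unrounded scores.

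| Diarrhoeal share | t-test, shift 1 | Wilcoxon, shift 1 | t-test, shift 0.5 | Wilcoxon, shift 0.5 |
|---|---|---|---|---|
| 50% | 5% | 6% | 5% | 5% |
| 60% | 10–11% | 19–21% | 6–7% | 9–10% |
| 70% | 27–30% | 56–61% | 10–11% | 19–23% |
| 80% | 58–64% | 89–92% | 17–19% | 39–43% |
| 90% | 91–94% | 99–100% | 37–41% | 62–66% |
| 100% | 100% | 100% | 83–88% | 82–86% |

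A t-test on |score − 4| has about 100% power at every share for a shift of 1, and 80–86% for a shift of 0.5. By symmetry the same figures hold with the two subtypes exchanged.

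These powers are for raw scores at one visit. Changes from baseline would remove most of the added spread in step 2 but not the dilution in step 1, which is still complete at 50:50.

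**Step 4, the normal-stool definition.** Its frequency part sets an upper limit (3 per day) and no lower one, so infrequent stools pass that part. The form part is separate and must also be met.

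**The case against.** **Bristol might be analysed as categories.** The article does not say whether a seven-type scale counts as continuous or categorical. A test of the distribution over types does not cancel: under the same assumptions a chi-square test has more than 99% power for a one-type shift at every mix, and about 50–60% for a half-type shift. This stands, so the point on Bristol is conditional on continuous treatment. Such a test still does not show whether a difference is benefit. Weekly frequency is a count and has no such route.

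**The subtype analysis is already planned.** If subtypes were evenly split, 77/4 gives about 19 per arm in each. Under the same inputs that gives roughly 81–85% power within one subtype for a one-type shift, unadjusted for multiplicity, and about 30% for half a type. So the subgroup analysis has real value, but it is not tied to these outcomes and leaves the pooled test as their stated analysis.

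**Detail may be in the SAP.** Score derivation often is. Here, however, the article itself names the measures and the tests, and the combination suits a one-directional scale.

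**Stronger readings that the article does not support.** A reader might infer that the effect must vanish. That needs a near-balanced mix with similar opposite shifts, and the article gives no expected mix. A reader might also infer that constipated patients always satisfy the normal-defecation definition. They do not, because a smooth, soft stool is required as well; only the frequency part is open at the lower end.

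**Conclusion.** The point holds in conditional form. If Bristol score is treated as continuous, it and weekly frequency are compared by pooled directional tests in a population where benefit has two directions. The loss runs from none (one subtype) to complete (an even split), with the t-test hit harder than Wilcoxon in unbalanced mixes. At any mix, the sign of a significant pooled result cannot be read as benefit or harm.

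The power figures rest on the assumed means, SD and equal shifts, and leave out mixed and unclassified IBS. For weekly frequency the reasoning is the same, but no power was computed. The primary outcome and the other secondary outcomes each run in one direction and are untouched. This should be corrected, but it does not threaten the main conclusion of the trial.

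**What to change.** - **Bristol, overall comparison:** analyse the absolute distance from type 4, adjusted for its baseline value, or the proportion of patients with the normal stool form that the frequency section already describes.
- **Weekly frequency, overall comparison:** analyse the distance outside a prespecified normal range that has a lower as well as an upper limit. The investigators need to set and justify that range.
- **Signed changes in form and frequency:** report them only within the constipation and diarrhoea subtypes, and state that the planned subgroup analysis covers these two outcomes.
- State whether Bristol score is handled as continuous or categorical.

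The cost is a changed derivation from data already collected, with no extra visits or patients. The article places the trial in its preparation phase, so the change can be made before any data are seen. The drawback is that the overall result is no longer in raw Bristol units or stool counts; the within-subtype results keep those units.
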